#### Thematic analysis (Aim 2)

Thematic analysis will be employed to guide qualitative data collection and simultaneous, iterative analysis to identify themes within the data [50]. Transcripts will be reviewed multiple times by co-authors to draw on key codes, and analysis will be completed once themes reach saturation [51]. Analysis will also disaggregate responses by age, gender, racial group, sexual orientation, and drug-using behavior to identify similarities and conflicting perspectives. Respondent verification, constant comparative analysis, and multiple coding will be employed in the analysis [52, 53].

#### Longitudinal analysis of time-updated overdose data (Aim 3)

Using OCC and TPaS data, the influence of DCS on the annual incidence of fatal and non-fatal overdose events will be characterized, while adjusting for underlying trends over time. Following others [54], conditional fixed effects Poisson models will be employed to test overdose incidence counts in geographic units that do and do not have DCS present, while adjusting for the presence of SCS. This approach allows for assessment of the estimated effect of DCS by analyzing the fluctuation in incidence rates in areas before and after DCS implementation, and by then comparing the relative change in incidence to other geographic areas. Disentangling the independent effects of DCS from those of SCS presents analytic challenges. However, SCS in Toronto were operational before DCS. This stepwise implementation represents an ideal natural experiment to assess the independent effect of DCS.

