#### SCS client survey data (Aim 1 substudy)

An ongoing longitudinal cohort is collecting data from people who inject drugs who do and do not use SCS at the three frontline agencies participating in the DCS network. This allows for harmonization of survey tools across both projects. As such, for participants consenting to linkages, data from a standardized SCS cohort survey (e.g., age, gender, neighborhood of residence, and drug-using factors) and data from the SCS pre/post injection assessment form (e.g., overdose outcomes, whether emergency medical attention was provided [i.e., SCS staff response and/or call to 911 for paramedic response], naloxone administered) will be accessible for consenting participants. This will also allow for a substudy consisting of a comparison of outcomes (i.e., overdose incidence and related risk behaviors) among frontline agency clients who access SCS exclusively, who access both SCS and DCS, and who access neither.

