#### Spatial patterns of fatal and non-fatal overdose in Toronto (Aim 3)

Employing approaches previously used to assess the association between risky drug-related behaviors and frontline services [55], data from the OCC and TPaS will be used to assess the spatial association between frontline harm reduction agencies with DCS and overdose events. This will be done by comparing geographic units that have DCS and SCS co-located with sites that only have SCS located, compared with sites that have neither. Changes over time in the incidence of overdose in these units will be determined by employing geographic information systems approaches. First, spatial buffers around each DCS site will be generated, and TPaS and OCC data will be used to capture the spatial location of non-fatal and fatal overdoses in surrounding areas. Significance testing will then be done by analyzing dissemination blocks (the smallest geographic unit defined by Statistics Canada with a population of 400–700 people). Toronto experienced 1542 non-fatal and 111 fatal overdoses over a recent 6-month period (August 2017–February 2018), and based on existing spatial data, it is estimated that the range of annual overdose events per dissemination block will range from 0 to > 100. This exploratory approach represents a simple descriptive test to determine the spatial correlation of overdoses and DCS. Second, to further account for potential confounding of the association between DCS and spatial patterns of overdose as a result of co-location of SCS and DCS [56], the mean distances between fatal overdoses (OCC data) in neighborhoods in which SCS are implemented but have not yet implemented DCS will be compared. Third, geographically weighted regression (GWR) will be employed to determine the spatial heterogeneity between the location of overdoses (dependent variable) and location of DCS (independent variable), while accounting for the presence of SCS as above. GWR calculates local spatial statistics by fitting a weighted regression equation for each dissemination block in the study area to assess local variation [57]. Local statistics will then be compared with the global statistic for the entire geographic area (i.e., the Province of Ontario), and blocks exhibiting local variation differing from the global statistic will be identified (including by undertaking a sub-analysis restricted to blocks within the City of Toronto). Using GWR, it will be determined whether those blocks exhibiting local variation in overdose incidence are more or less likely to also contain DCS. Fourth, the local annual incidence rate of overdose for each block will be determined. The Wilcoxon signed rank-test has previously been shown to be effective at assessing fluctuations in the annual rate of fatal and non-fatal overdose [56], and will allow a determination of slope differences in the overdose rate in blocks that do and do not have DCS.

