DCS in Toronto have been integrated within public health and community health agencies with existing SCS, thereby combining harm reduction service delivery with access to other services including primary care, mental health care, social service programs, and scientific evaluation. The implementation of DCS will allow frontline harm reduction agencies to extend their services by providing clients with timely information on the composition (qualitative and quantitative) of their drugs. While DCS are not a panacea for drug-related harms, increasing information on the unregulated drug supply may disrupt the risk environment for people who use drugs by equipping them with tailored and highly relevant information related to their substance use, as well as by increasing transparency and accountability in the drug market by reducing information asymmetries between buyers and sellers throughout the supply chain. Evidence from European DCS indicates that DCS benefits can extend beyond those individuals that engage directly with the service, as analysis results are often communicated to others, thus multiplying the preventive effect for a broader population of people who use drugs [65]. Although DCS can play an important role in drug market monitoring and therefore have the potential to influence drug market activities, the absence of legally regulated markets for illegal drugs creates a paradox wherein people who use drugs may become aware of dangerous adulterants in their drugs but have no viable option for the replacement of the analyzed substance. Particularly for those facing intersecting vulnerabilities such as poverty and substance-use disorders, increased information on substance composition may be insufficient to modify their risk environment. In cases where information from DCS does not effectively reduce overdose risk for clients, other policy approaches and interventions—such as scaling up low-barrier access to managed opioid programs—should be considered. Importantly, DCS have the potential to attract clients who may otherwise not access drug-related services—as has been demonstrated by DCS in Europe [18, 22, 66]—and given the co-location of DCS with other services, DCS may support increased uptake of other harm reduction, primary care, mental health care, and social services among people who use drugs. While such an integrated model of harm reduction services offers the promise of a “one-stop shop” with the potential to improve health outcomes for people who use drugs, drawbacks such as reduced anonymity may pose barriers for some clients. Accompanying evaluations of DCS and SCS will examine different models of service provision, under what conditions benefits can be maximized, suitability for specific subpopulations, and a variety of indicators including successful referrals to other services.

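### The area-level Poisson model takes a change in overdose counts near DCS sites as the DCS effect, but names no adjustment for a DCS-related shift in where people use drugs

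*Protocol article*

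**What the plan says.** The Protocol article, under Longitudinal analysis of time-updated overdose data (Aim 3), plans conditional fixed effects Poisson models "to test overdose incidence counts in geographic units that do and do not have DCS present". Two adjustments are named: "while adjusting for underlying trends over time" and "while adjusting for the presence of SCS". The DCS effect is to be assessed by "analyzing the fluctuation in incidence rates in areas before and after DCS implementation" and comparing the relative change with other areas. The section describes the introduction of SCS first and DCS later as an ideal natural experiment, and the Limitations section says so again.

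The outcome data are coroner and paramedic records, which carry the location of the event. The section on spatial patterns adds that "the local annual incidence rate of overdose for each block will be determined". Neither section names the denominator of its rate.

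Three other places bear on where drug use occurs once DCS opens:
- Results: "DCS have the potential to attract clients who may otherwise not access drug-related services". The same discussion says co-location may increase uptake of other harm reduction services.
- Table 1, Aim 1: use of SCS is one of the protective behaviors whose increase is an outcome.
- SCS client survey data (Aim 1 substudy): the response to an overdose in an SCS can include a call to 911 for paramedics.

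The Limitations discuss separating SCS from DCS effects. They do not mention a change in where people use drugs.

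**The concern.** A ratio of counts by location equals a ratio of individual risks only if DCS does not itself change how many people use drugs in the unit. The article gives two reasons why it might: DCS may reach people who were not using services, and it may increase use of an SCS inside the same unit. An overdose that would have occurred elsewhere in the city would then be recorded in the DCS unit.

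The stated adjustments do not absorb this:
- Unit fixed effects remove population differences that are constant over time. The shift in question begins with DCS.
- A time trend shared across units cannot capture a change confined to DCS units.
- A term for SCS presence does not change when more people use an SCS that is already open.
- A fixed census population as offset has no effect, because the unit fixed effects already absorb it.

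A service that lowers its clients' risk could therefore show no change, or an increase, in its own area. This is the planned area-level test of DCS on recorded overdoses, so such a result could mislead decision makers.

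**Working it through.** The article states no effect size or power for this model, so there is no figure of the plan to reproduce.

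**Inputs from the documents.** Estimated overdose incidence (Aim 3): 1002 paramedic calls in 2018 in neighborhoods adjacent to the three sites, 31% of the city total. Spatial patterns section: 1542 non-fatal and 111 fatal overdoses in the city in six months.

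**Input check.** City calls per year = 1002 / 0.31 = 3232. Doubling the six-month figure gives 2 × (1542 + 111) = 3306, about 2% higher, so the sources agree. Calls elsewhere = 3232 − 1002 = 2230.

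**Assumptions, not in the documents.** True individual risk ratio RR = 0.85; relative inflow g = 10% or 20%; one year before and one year after; no overdispersion; the 1002 calls taken as the DCS-unit baseline, since the article does not fix the unit.

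**Step 1: inflow alone, control areas flat.** Observed ratio = RR × (1 + g).
- g = 10%: 0.85 × 1.10 = 0.935
- g = 20%: 0.85 × 1.20 = 1.02
- Inflow that hides the benefit completely: 1/0.85 − 1 = 17.6%. For RR 0.80 it is 25%, and for RR 0.90 it is 11%.

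**Step 2: inflow drawn wholly from the control areas.**
- g = 10% moves about 100 calls. Controls fall to (2230 − 100)/2230 = 0.955, and the contrast becomes 0.935/0.955 = 0.98.
- g = 20% moves about 200 calls. Controls fall to 0.910, and the contrast becomes 1.02/0.910 = 1.12.

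On the log scale the bias at g = 10% rises from ln(1.10) = 0.095 to ln(1.10/0.955) = 0.141, a factor of about 1.5.

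**Step 3: size against sampling error.** SE(log ratio) = √(1/1002 + 1/(1002 × ratio) + 2/2230). At a ratio of 1 this is 0.054, so a 10% inflow with flat controls is 0.095/0.054 = about 1.8 standard errors of the planned contrast. The chance of a significant benefit (two-sided 0.05) at RR 0.85 is 83% with no inflow (log ratio −0.163, SE 0.055), 23% at 10% (−0.067, SE 0.054) and 1% at 20% (+0.020, SE 0.054). Ignoring overdispersion makes the 83% optimistic.

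**Step 4: what a wider unit shows.** Suppose the wider unit holds 2004 calls (an assumed 2 × 1002), all movement stays inside it, and only those using drugs near the sites benefit. Its ratio is 1 − 0.15 × 1002 × (1 + g)/2004.

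| | Site-adjacent unit (controls as in Step 2) | Wider unit |
|---|---|---|
| g = 0 | 0.85 | 0.925 |
| g = 10% | 0.98 | 0.918 |

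Without movement, the wider unit gives the weaker effect through dilution. With movement, the order reverses. That comparison is the diagnostic.

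**The case against.** The strongest reply is that the article predicts no migration. The Results sentence speaks of potential and concerns contact with services; those people may already live or use drugs nearby. The Sample size section derives its 1080 DCS clients from 1800 people said to access frontline agencies already, and the neighborhoods concerned already have the greatest density of people who use drugs. A DCS visit means handing over a sample, with results one to two business days later in person or by phone, and neither step requires using drugs near the site. SCS, which does bring consumption on site, opened about a year earlier, so much of any draw predates DCS. All of this stands, and it means the inflow could be small or nil. It does not remove the route through greater use of the co-located SCS, which the article counts as a success.

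A second reply is that the article speaks of incidence rates and that an offset may be set out in a document not shown. That is fair, and a missing offset is not the point here. The point is the inference the article does state, from a relative change in counts to a DCS effect. A census offset would not repair it.

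A reader might go further than the documents allow:
- *That the protocol expects people to move into DCS areas.* It states only a possibility of reaching new clients.
- *That the model takes no account of population.* Fixed effects handle constant differences; only change over time is uncovered.
- *That losses from control areas double the bias.* On the article's call figures the factor is about 1.5, because the control areas hold more than twice the calls.
- *That a 10% inflow is three standard errors.* That divides about 100 calls by √1002 = 32, the error of a single yearly count. For the planned contrast it is about 1.8 with flat controls.

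**Conclusion.** The point holds in a limited form. The model counts overdoses by location and names no adjustment for a change over time in the number of people using drugs in a unit. If DCS shifts drug use into its own units, the count ratio is biased toward no benefit by the factor (1 + g), and by more if the inflow comes from the control areas. If it shifts drug use out, the bias runs the other way. With a true ratio of 0.85, an inflow of about 18% would hide the benefit entirely. Both the 0.85 and the inflow sizes are assumptions, so the documents support a plausible bias of unknown size, not a demonstrated one.

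The outcome labelled primary, self-reported overdose in the Aim 1 survey, and the individual-level SCS substudy do not depend on area counts and are unaffected. What is affected is the claim that the staged opening of SCS and DCS isolates the DCS effect in the coroner and paramedic data.

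**What to change.** Keep the site-adjacent analysis and run the same Poisson model in parallel with a wider treated unit, so that movement within it cancels. Fix that unit before the outcome data are examined, for example as larger buffers around the sites, or as the neighborhoods where SCS cohort members lived before DCS opened. The cohort survey records the field ("e.g., age, gender, neighborhood of residence, and drug-using factors"). Report the two estimates side by side and say in advance how they will be read: a wider-unit effect as strong as or stronger than the site-adjacent one suggests that events moved. Add one sentence to the longitudinal analysis section and one to the Limitations saying that a count change near a site is not by itself a change in individual risk.

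The cost is modest: redefined units and one more model on data already to be obtained. The wider unit dilutes a purely local effect, so it should be a sensitivity analysis and should not replace the site-adjacent unit. Movement from beyond the wider unit does not cancel. Residence data cover only linked, consenting SCS cohort members who inject drugs, which favors the buffer definition. The wider unit should not be built from the residences of observed DCS clients, because it would then be defined after treatment.

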## Background

The increasing incidence of fatal opioid overdose is a public health crisis in Canada. From January to September 2018, there were 3286 opioid-related deaths in Canada, corresponding to a death rate of 11.8 per 100,000 population (compared to 11.1 and 8.4 per 100,000 population in 2017 and 2016, respectively) [1]. In the western province of British Columbia, opioid overdose deaths have contributed to a decline in life expectancy, particularly among the most socioeconomically disadvantaged and marginalized communities [2]. In the province of Ontario, opioid overdose is now the leading cause of accidental death for young people, with one of every eight deaths among individuals aged 25 to 34 years involving an opioid [3]. With 308 opioid-related deaths in 2017, the country’s largest city, Toronto, Ontario, has experienced a 125% increase in deaths compared to 2015 [4]. There is now a consensus that the rising incidence of overdose is related in large part to the emergence of highly potent opioids, such as fentanyl and fentanyl analogs, in the unregulated drug supply. For example, fentanyl is present in an increasing number of overdose fatalities in Canada, though overdose deaths excluding fentanyl have remained relatively stable [5]. In Ontario, the presence of fentanyl in opioid-related deaths increased by 548% between 2006 and 2015 [6]. In 2017, there were 1265 opioid-related deaths in the province and fentanyl was present in 63.6% of these deaths; in contrast, fentanyl was present at death in 40.7% of 867 opioid-related deaths in 2016 [7]. This trend has thus accelerated in recent years, and fentanyl has overtaken heroin as the opioid most commonly present in opioid overdose deaths in Toronto [4]. In response, Canada’s federal government has characterized the current situation as a national public health crisis and allocated CAD$116 million in 2017 to a public health emergency response coordinated by Health Canada [8, 9], while the Government of Ontario committed CAD$280 million over 3 years to address the opioid overdose crisis [10].

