#### Estimated overdose incidence (Aim 3)

While no formal estimates of the overdose rate among people who use drugs in Toronto have been derived, 1002 overdose calls (fatal and non-fatal combined) were made to Toronto Paramedic Services between January 2018 and December 2018 in neighborhoods adjacent to the three frontline DCS sites, representing 31% of all calls across Toronto [49]; these neighborhoods are also those with the greatest density of people who use drugs [35]. We also note that the incidence of > 1000 overdose events recorded near DCS sites implies a relatively high event rate among potential DCS clients.

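### The Aim 3 Poisson comparison sets the highest-density areas against unspecified other areas with no safeguard against differing background trends, so calling it an ideal natural experiment is too strong

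*Protocol article*

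**What the plan says.** The section on longitudinal analysis of overdose data (Aim 3) in the protocol article uses coroner and paramedic data and states that "conditional fixed effects Poisson models will be employed to test overdose incidence counts in geographic units that do and do not have DCS present". Two adjustments are named: "while adjusting for underlying trends over time" and "while adjusting for the presence of SCS". The effect is taken from the change in DCS areas from before to after implementation, "by then comparing the relative change in incidence to other geographic areas". Because SCS opened first, the section concludes: "This stepwise implementation represents an ideal natural experiment to assess the independent effect of DCS". The Limitations section repeats this view and puts the gap between the two services at one year.

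The section on estimated overdose incidence describes the treated areas. In 2018, "1002 overdose calls (fatal and non-fatal combined) were made to Toronto Paramedic Services" from neighborhoods adjacent to the three sites. That was 31% of all such calls in the city, and "these neighborhoods are also those with the greatest density of people who use drugs".

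**The concern.** The contrast is a difference-in-differences on the log rate. It estimates the DCS effect only if, without DCS, the DCS areas and the comparison areas would have changed by the same proportion. Area fixed effects take out any stable difference in level. They do nothing about a difference in slope.

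The DCS areas are a selected, extreme group, and the Background describes a fast-moving epidemic: Toronto deaths rose 125% from 2015 to 2017. If the high-density areas were reached earlier, peaked earlier or worsened faster than the rest, their trend would differ for reasons unrelated to DCS. An earlier plateau there would look like prevention; a faster rise would look like harm or would hide a benefit.

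The order of implementation helps to separate DCS from SCS. It says nothing about where DCS was placed, so this problem would remain even if SCS had no effect at all. The Limitations section covers the SCS overlap but not the comparability of areas.

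**Working it through.** **Plan's own figure.** The article gives no effect size, power or error rate for this analysis, so there is none to reproduce. The event counts can be checked against each other:

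- Estimated overdose incidence section: 1002 calls at 31% imply 1002 / 0.31 = 3232 city calls, hence 3232 - 1002 = 2230 outside the DCS neighborhoods.
- Spatial patterns section: 1542 + 111 = 1653 events in six months, or 3306 a year; 1002 / 3306 = 30.3%. The two sources roughly agree.

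**Assumptions (not in the documents).** Years 2017-2020; SCS from 2018 and DCS from 2019 (the launch year and one-year gap are in the article); 20% of outside events in SCS-only areas (0.20 x 2230 = 446 a year); log-linear trends; true DCS rate ratio 1; trend in DCS areas differing from the other areas by d per year.

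**Hand calculation without the SCS term.** With two years before and two after, the expected estimate is

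[(1+d) + (1+d)^2] / [(1+d)^-1 + 1] = (1+d)^2.

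So d = -5% gives 0.95^2 = 0.90; -10% gives 0.90^2 = 0.81; +5% gives 1.05^2 = 1.10; +10% gives 1.10^2 = 1.21. The level of the rate cancels; the slope does not.

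**Model as described.** Poisson regression with unit fixed effects (same point estimate as the conditional form), common year effects, an SCS indicator and a DCS indicator, fitted to expected counts:

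| Trend difference per year | Estimated rate ratio (truth 1) | z |
|---|---|---|
| -10% | 0.830 | -4.3 |
| -5% | 0.913 | -2.1 |
| 0 | 1.000 | 0 |
| +5% | 1.091 | 2.1 |
| +10% | 1.185 | 4.1 |

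The z values assume pure Poisson variance and would shrink with overdispersion.

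**Does the SCS term cure it?** No. Even if SCS-only areas share the trend of the DCS areas, the estimates are 0.902 and 1.098 at -10% and +10%.

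**Can it hide a benefit?** Yes. A true ratio of 0.90 with a +10% trend difference is estimated as 1.066.

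**Longer window.** With 2015-2022, the results at -10% and +10% are 0.694 and 1.400.

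**What the remedies do.**

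- A linear trend specific to DCS areas returns 1.000 at every difference tested. The log-scale standard error rises from about 0.042 to about 0.087.
- Restricting controls to SCS-only areas returns 1.000 if those areas share the DCS-area trend, with a standard error of about 0.055-0.061. At d = 0: sqrt(2/2004 + 2/892) = 0.057, where 2004 and 892 are two years of events in each group. If SCS-only areas do not share that trend, the estimate is again (1+d)^2, which is why the trend check is needed as well.

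**The case against.** The article condenses its methods into one paragraph and cites a precedent that is not shown. Which units enter the control pool, and what form the trend term takes, could reasonably be settled elsewhere. A reader might infer that every other area serves as control. The text does not say so; it only states no restriction. The trend adjustment could also be area-specific, which would remove the bias in the illustration. These points stand, and they are why the bias is conditional.

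The spatial analysis section does use more comparable groups: DCS with SCS, SCS only and neither, as well as neighborhoods with SCS but not yet DCS. It also looks at slope differences between blocks with and without DCS. This shows awareness of the issue, but these are separate analyses. The first step is called exploratory and descriptive, and the second compares distances between fatal overdoses. None defines the Poisson control set.

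A reader might also try to size the bias from the Background, for instance from "In 2017, there were 1265 opioid-related deaths in the province and fentanyl was present in 63.6% of these deaths" against 867 the year before, set beside the rise in the national death rate. That does not work: it compares counts with a rate, Ontario is part of Canada, and neither is a Toronto neighborhood.

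Finally, parallel trends is a standard caveat for any such design, and the declared primary outcome is self-reported overdose under Aim 1. That limits the weight of the point. It remains a point because the article does more than stay silent: it asserts that the design is ideal for isolating the DCS effect.

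**Conclusion.** The point holds in conditional form. The article documents that DCS sits in the areas with the greatest density of people who use drugs, identifies the effect against areas without DCS, and names no safeguard against a differing trend. The stated fixed effects, SCS term and trend adjustment, as worded, do not ensure that such a difference is removed.

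The documents do not show that neighborhood trends differ, so it cannot be said that the result will be biased, or in which direction. Under the assumptions above, a gap of 5% per year would move a null ratio to about 0.91 or 1.09, and 10% to about 0.83 or 1.19. With no gap there is no bias, however different the levels. This limits what the Aim 3 analysis may conclude and is worth correcting. It does not invalidate the study.

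**What to change.** In the Aim 3 longitudinal analysis section:

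1. Make the main comparator SCS-only units, or other high-incidence units similar to the DCS areas in pre-DCS overdose level and trend, by matching or weighting. Keep the unrestricted comparison as secondary.
2. Report lead estimates (pre-DCS period by DCS area) with confidence intervals. Use periods shorter than a year, since the data-sharing agreements cover temporal information, and separate periods before and after SCS opened. With annual data the last pre-DCS year is also the SCS start-up year, so a lead could reflect SCS. Judge the leads by their size and interval, not by whether they equal 1 exactly.
3. Add a sensitivity model with a DCS-area-specific trend.
4. State the DCS effect as causal only if it is consistent across these analyses; otherwise report an association.
5. Soften the natural-experiment wording here and in Limitations, and add comparability of areas to the limitations.

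The data already fall under the coroner and paramedic agreements, so the cost is analysis time and precision. In the illustration the log-scale standard error goes from about 0.04 to about 0.06 with SCS-only controls, or 0.09 with the area-specific trend. Close matches may be few, because the DCS areas are the extreme of the distribution; if so, the report should say so and claim only an association.
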